#### Self-reported physical activity

To complement wearable-derived data and assess convergent validity between objective and subjective measures of physical activity, participants will complete two validated, self-report instruments. Specifically, the Physical Activity Scale for the Elderly (PASE; [22]) will be administered at week 0 (baseline) and week 8 (post-intervention). This questionnaire will capture the frequency, duration, and intensity of physical activity over the prior 7 days. In addition, participants will complete the Community Healthy Activities Model Program for Seniors (CHAMPS) questionnaire, which evaluates the effectiveness of an exercise intervention in community-dwelling older adults. From the CHAMPS questionnaire, a Metabolic Equivalent of Task (CHAMPS–MET) metric will be derived; this metric will be utilized to estimate weekly caloric expenditure [23]. The CHAMPS survey will also be administered at week 0 (baseline) and week 8 (post-intervention). The integration of these two tools will enable a comprehensive triangulation strategy to optimally evaluate alignment and potential discrepancies between perceived and actual physical activity. Discrepancy scores between self-reported and Fitbit data will be computed and examined as potential moderators or mediators of outcomes, particularly in relation to cognitive status and/or adherence.

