#### Continuous physical activity monitoring

Participants will wear a Fitbit continuously throughout the study, including during both wake and sleep hours. Fitbit-derived data will be categorized into three activity domains:Protocol-Guided Exercise (PGE): Exercise occurring during supervised, in-lab sessions.Non-Protocol Physical Activity (NPA): Incidental movement and unsupervised activity outside scheduled sessions.Total Physical Activity: Combined PGE + NPA, derived from 24-h Fitbit data.

The primary Fitbit metric will be daily step count, a validated proxy for global movement shown to correlate with cognitive, brain, and cardiometabolic health outcomes in older adults [37]. A secondary metric, calories burned, will offer insight into the metabolic intensity of movement. Step count and caloric expenditure will be examined in relation to cognitive function as well as brain and cardiometabolic biomarker outcomes. Analytical models will include PGE and NPA as independent predictors, which will be modeled separately and jointly to assess differential and additive contributions to primary (cognitive, brain, and cardiometabolic markers), secondary (sleep metrics and exercise measures), and tertiary (light exposure and psychosocial measures) outcomes.

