#### Physical Activity Scale for the Elderly (PASE) questionnaire

The PASE Questionnaire will only be administered to participants assigned to interventions involving exercise. The PASE is a validated, self-report instrument that is widely used to assess physical activity. The PASE Questionnaire was originally designated for community-dwelling adults aged ≥ 65 years but has been subsequently validated in adults aged 45–64 years [45]; this questionnaire has demonstrated high test-retest reliability, with intraclass correlation coefficients (ICC) found to be *r* = 0.75 (95% CI = 0.69–0.80) over 3–7 weeks [22]. Short-interval reliability (10–14 days) has shown excellent reproducibility with ICCs, which range from 0.93–0.99 in prior work [46, 47]. Furthermore, construct validity is moderately supported: correlations with accelerometer-measured physical activity (steps, energy expenditure) range from *r* ≈ 0.30–0.61 [48]. While internal consistency varies across activity domains (α ≈ 0.69–0.99 [22, 46]), the total score remains robust for classifying overall activity levels in older populations. Given the robustness of the PASE questionnaire across older adult populations, similar reliability is expected in upper middle-aged adults (55–64 years).

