#### Fitbit charge 5 wearable metrics

Consumer-grade Fitbit devices, including the Charge series, have demonstrated acceptable validity and reliability for measuring steps and energy expenditure in older adults. In controlled laboratory settings, Fitbit-measured steps agreed within ± 3% of observed counts; in free-living conditions, deviations remained within approximately ± 10% of research-grade accelerometers (e.g., actigraphy [51]). Prior evidence indicates that step counts correlate well with self-reported metrics—specifically, Fitbit steps with the PASE questionnaire and Fitbit calories burned with the CHAMPS–MET metric, particularly in older adult populations [37]. While Fitbit may underestimate steps at slower gait speeds [52], overall metrics are sufficiently reliable for longitudinal monitoring in aging cohorts. Data collection from this device will consist of two steps: (1) a period of data collection while participants initially wear the Fitbit for seven consecutive days before the intervention is implemented and (2) subsequent data collection while participants continue wearing the Fitbit throughout the intervening period. Similarly to the interventions that include exercise, participants in the sleep-only group will also be asked to continuously wear the device throughout the 8-week trial duration to ensure that physical activity levels do not confound the effects of sleep.

It should be noted that there is a considerable paucity of evidence in the prevailing body of literature assessing how well Fitbit-derived metrics correlate with PASE and CHAMPS-MET scores in upper middle-aged adults (i.e., 55–64 years). As a result of this age-specific validation gap, the current trial will combine Fitbit metrics (e.g., step counts and caloric expenditure) with self-reported physical activity data from the PASE and CHAMPS questionnaires; this approach will enable a more comprehensive assessment of physical activity patterns and provide an opportunity to compare and interpret agreement between objective and self-reported measures within this cohort. The paucity of evidence that has assessed these correlations with the inclusion of middle-aged and older adult samples has generally found moderate relationships between Fitbit-derived step counts and PASE scores as well as between Fitbit-derived estimated energy expenditure and CHAMPS-derived MET values [37].

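### If the self-report versus Fitbit discrepancy score is built as a difference, it mixes misperception with activity level, so the Fitbit measure and its interaction belong in the same model

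*Protocol article*

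**What the plan says.** Under Self-reported physical activity, the article sets PASE and CHAMPS beside the Fitbit data in order to "evaluate alignment and potential discrepancies between perceived and actual physical activity". It then commits to a use: "Discrepancy scores between self-reported and Fitbit data will be computed and examined as potential moderators or mediators of outcomes", with cognitive status and adherence singled out. It gives no formula, pairing, scale or visit for the score.

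The measures are described in several places:

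- **Fitbit.** Continuous physical activity monitoring states that "The primary Fitbit metric will be daily step count" and that "A secondary metric, calories burned, will offer insight into the metabolic intensity of movement".
- **PASE.** The instrument section treats it as a scale, saying that "the total score remains robust for classifying overall activity levels in older populations". It reports that "correlations with accelerometer-measured physical activity (steps, energy expenditure) range from" about 0.30 to 0.61.
- **CHAMPS-MET.** Of this metric the article says that "this metric will be utilized to estimate weekly caloric expenditure". The CHAMPS section quotes correlations of about 0.23 to 0.55, against accelerometer measures or functional health indicators.
- **Pairing.** The Fitbit section reports earlier evidence linking "Fitbit steps with the PASE questionnaire and Fitbit calories burned with the CHAMPS–MET metric".

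The covariates listed under Adherence and engagement include baseline physical activity and cognitive status. PASE and CHAMPS are given only to the two arms that include exercise, so the score can exist for about 40 of the 60 participants.

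**The concern.** A difference between two imperfectly correlated measures is negatively related to the one that is subtracted, unless the other measure has a sufficiently larger spread. A participant with high Fitbit activity will tend to have a low value of self-report minus Fitbit even if nobody misjudges their activity in any systematic way. Used as a moderator or mediator without Fitbit activity beside it, the score can pick up an effect that belongs to activity.

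The risk is greatest where the article points the analysis. If participants with MCI, or poor adherers, differ in activity level (the documents do not say whether they do), that difference could be reported as a difference in how well they perceive their activity. The pilot is meant to inform a larger trial, so a mislabelled signal would carry forward.

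**Working it through.** The plan states no figure for the score, so there is nothing to reproduce. The check uses the algebra of a difference.

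**Set-up.** Let S be self-report, F the Fitbit measure, r their correlation, k = SD(S)/SD(F), and D = S - F. Then

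corr(D, F) = (rk - 1) / sqrt(k² + 1 - 2rk).

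**z-score difference (k = 1).** This reduces to corr(D, F) = -sqrt((1 - r)/2). The r values come from the PASE and CHAMPS sections.

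| Source of r | r | (1 - r)/2 = variance shared with F | corr(D, F) | corr(D, outcome) = 0.4 × corr(D, F) |
|---|---|---|---|---|
| PASE, low | 0.30 | 0.350 | -0.59 | -0.24 |
| PASE, high | 0.61 | 0.195 | -0.44 | -0.18 |
| CHAMPS, low | 0.23 | 0.385 | -0.62 | -0.25 |
| CHAMPS, high | 0.55 | 0.225 | -0.47 | -0.19 |

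The last column assumes that activity correlates 0.4 with the outcome and that self-report has no effect of its own. If the assumed correlation is 0.3 to 0.5, the score correlates -0.13 to -0.31 with the outcome. It would then be significant at two-sided 0.05 in 13% to 50% of trials with n = 40 when used alone (Fisher z), against a nominal 5%.

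**Raw difference.** The article does not give k, so these are ranges under assumption.

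- PASE minus steps, with k of 0.005 to 0.02 (a scale score against thousands of steps): corr(D, F) is about -1.00. The score is steps with the sign reversed.
- CHAMPS minus Fitbit calories, on a common period: -0.88 to -0.87 at k = 0.5, -0.41 to -0.14 at k = 1.5, and -0.27 to +0.06 at k = 2. It is exactly zero at k = 1/r, that is 1.8 to 4.3.

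**Moderation.** A bivariate correlation does not by itself produce a false interaction, so this was simulated separately: two arms of 20, a z-score difference, the Fitbit main effect already in the model, and an intervention effect modified by Fitbit activity alone. With slopes on activity of equal size and opposite sign in the two arms (assumed 0.3 to 0.5), the group-by-score term was significant in roughly 11% to 41% of trials across r = 0.61 and r = 0.30. With activity acting in one arm only, at the same slope, the excess was smaller, about 7% to 14%. Adding group-by-Fitbit brought the rate back to about 5% in every case.

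**Mediation.** The exercise arms target 270 minutes of moderate exercise a week, so Fitbit activity is meant to change during the trial and D changes with it. Adjusting for baseline activity does not separate the two.

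**With Fitbit activity in the model.** If Y = a + bD + cF, then Y = a + bS + (c - b)F. The coefficient of D is the coefficient of self-report, and the artefact is gone. In simulation with an outcome driven by F alone, that coefficient was about 0. A residual of S on F correlates 0.00 with F by construction.

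**The case against.** **Subtraction is not stated.** The article says only that scores will be computed. A residual would also be a discrepancy score and would be uncorrelated with Fitbit activity. The formula may sit in a fuller plan that is not shown. This stands: the point is conditional on a difference, and the absence of a formula is not itself an error.

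**A stronger reading is tempting.** A reader might infer that the plan subtracts measures with no common unit and that the score therefore does not measure misperception. The documents do not support that. CHAMPS-MET and Fitbit calories are both energy expenditure and can be put on the same period. Even for the z-score difference, about 61% to 80% of the variance is not shared with Fitbit activity. The score mixes the two things; it is not activity alone.

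**Fitbit activity is already a model term.** The article plans models with protocol-guided and non-protocol activity as predictors, and lists baseline activity as a covariate. If concurrent activity entered the same linear model as the score, the main-effect artefact would vanish. However, neither section says that these terms enter together with the score, and neither mentions an activity interaction, which is what a moderator analysis needs.

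**The inputs are approximate.** The PASE range is against accelerometers rather than Fitbit, and part of the CHAMPS range may be against functional indicators. The PASE figures are therefore the safer ones.

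**The analysis is exploratory.** No primary, secondary or tertiary outcome depends on the score. That limits the weight of the point but does not remove it.

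**Conclusion.** The point holds in a conditional form. If the discrepancy score is a difference, it confounds misperception with activity level. For z-scores the correlation with device activity is about -0.44 to -0.59 at the article's PASE correlations, and -0.47 to -0.62 at its CHAMPS range. A raw PASE-minus-steps score would be almost entirely steps. A raw calorie difference could go either way, depending on a ratio of spreads that the article does not give.

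The consequences for outcomes (-0.18 to -0.25) and for false interactions rest on assumed effects of activity, so they show what can happen and do not predict it. The covariates named in the article do not clearly protect the moderator or mediator analyses. The change is worth making, but it affects one exploratory derived variable and not the main group comparison.

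**What to change.** In these exploratory models, replace the difference by its components. Enter the Fitbit measure and the matching self-report measure together and, for moderation, give each its own interaction with group or cognitive status. For mediation, keep Fitbit activity over the same period in the model beside self-report. If a single discrepancy variable is wanted, define it as the residual of self-report regressed on Fitbit, and keep Fitbit activity, with its interaction where relevant, in the model. Attribute a result to misperception only if the self-report or residual term shows it with activity accounted for.

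The cost is one or two more terms in an exploratory model fitted to about 40 participants, with some loss of precision. No new data are needed.

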#### Biomarker collection strategy

Brain and cardiometabolic health will be assessed using a hybrid biospecimen collection protocol. Two venipuncture-based blood draws will be conducted through Quest Diagnostics, occurring at week 0 (pre-intervention) and week 8 (post-intervention) under standardized fasting conditions. To maximize participant safety and minimize all possible influences of acute exercise [20], pre-intervention blood draws will be obtained no later than 7 days prior to, but no sooner than 24 hours before, the initiation of the first exercise session, and post-intervention blood draws will be obtained within 24–48 hours after completion of the final exercise session. No blood draws will occur on the same day as in-lab exercise. For all participants, plasma samples will be assessed for cardiometabolic risk, which will include high-sensitivity C-reactive protein (hs-CRP), glycated hemoglobin (HbA1c), and fasting total cholesterol, high-density lipoproteins (HDL), low-density lipoproteins (LDL), triglycerides, insulin, and C-peptide levels, which will provide time-sensitive insight into the inflammatory, glycemic, lipid, and insulin resistance markers across the intervention period. Furthermore, the extent of AD-associated neuropathology will be assessed at baseline via plasma samples, which will include amyloid beta peptide 1–42 (Aß1–42), Aß1–40, Aß1–42/Aß1–40 ratio, and phosphorylated tau at threonine 217 (p-tau217). These biomarkers will be subsequently integrated into a single analytical interpretation of AD risk, which has an 88% positive and 91% negative concordance with amyloid-PET-based results [38]. The aforementioned biomarkers will serve as staging and stratification variables, enabling the utilization of such biomarkers as covariates or effect moderators (e.g., assessing whether intervention response differs by baseline pathology status) without presuming measurable longitudinal change over the short intervention window. Additionally, in order to capture biologically meaningful change over an 8-week duration, plasma neurofilament light chain (NfL) will be obtained and measured at baseline and at post-intervention. Unlike the amyloid- or tau-based biomarkers, NfL reflects ongoing neuroaxonal stress and overall neurodegeneration and has demonstrated sensitivity to behavioral and lifestyle interventions, including exercise- and sleep-related alterations, over relatively short time periods (e.g., 8 weeks) [39]. Consequently, NfL is more appropriate for detecting intervention-related biological signals within the timeframe of this pilot study.

#### Temporal synchronization and data integration

Physical activity, cognitive function, and biomarker data will be aligned using a centralized time-stamped database. Sampling windows will be synchronized with protocol events (e.g., in-lab sessions, assessment points) to ensure precise temporal integration of physiological, cognitive, and behavioral data streams.

#### Adherence and engagement

In order to assess adherence to the exercise sessions, attendance will be recorded for all in-person sessions, and wearable devices (Fitbit) will track daily physical activity, including steps, heart rate, and durations of physical activity. Weekly check-ins (10–15 minutes) via phone or secure teleconference will be conducted and documented to ensure protocol adherence, troubleshoot technical issues, and maintain engagement. All data will be stored in HIPAA-compliant systems. Fitbit and the Digital Neuro-Signature Platform data will be de-identified and linked using secure participant codes. Statistical models will include age, sex, years of educational attainment, employment status (unemployed/employed), socioeconomic status, baseline sleep metrics, baseline physical activity levels, and cognitive status as covariates. By integrating standardized, in-lab exercises, wearable technology, digital cognitive assessments, and multimodal biomarker data, this arm of the *CASE* study aims to explore the cognitive, brain, and cardiometabolic impacts induced by structured exercise in aging adults who are at higher risk for AD using a real-world, ecologically valid framework.

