## Methods

### Study design overview

*Combating Alzheimer’s through Sleep and Exercise (CASE)* is a single-center, three-arm, randomized trial that will investigate the effects of sleep, exercise, and a combination of these on cognitive function as well as brain and cardiometabolic biomarker outcomes in older adults with and without MCI. Participants will be randomly assigned via Research Electronic Data Capture (REDCap [18, 19]) to one of three groups: (1) exercise-only, (2) sleep-only, or (3) combined sleep and exercise. Each group will receive the following intervention-specific digital tools: (1) all groups will receive a Fitbit to continuously track physical activity, including the tracking of all in-person, biweekly, 60-minute exercise interventions; (2) the sleep-only and sleep + exercise groups will receive the Elemind Neuromodulation headband for personalized acoustic stimulation; and (3) the sleep-only and sleep + exercise groups will receive a Lys device for monitoring light exposure.

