Individuals meeting these pre-screening criteria will then be scheduled for an in-person screening visit to provide written informed consent and further assess eligibility criteria via a 7-day screening period. After signatures are obtained, each prospective subject will be provided with a copy of the signed informed consent document. All procedures have been approved by the University of Miami Institutional Review Board (IRB) requirements and federal privacy protections and will be conducted in accordance with the Helsinki Declaration. Thereafter, prospective participants will be randomized into one of three arms and will receive intervention-specific, wearable devices and will be instructed on how to use these devices. All prospective participants will receive Fitbit devices, while those assigned to sleep or sleep + exercise intervention will receive an Elemind Neuromodulation headband to be used daily without stimulation during the initial 7-day screening period and a Lys device. Prospective participants in all groups will be asked to wear the Fitbit device continuously to establish baseline physical activity levels and to confirm sedentary to lightly active physical activity levels in order to satisfy eligibility criteria for those assigned to interventions that involve exercise, and those assigned to the sleep-only or sleep + exercise interventions will be asked to wear the Elemind Neuromodulation headband without stimulation while the device actively collects sleep data for seven consecutive nights to establish baseline sleep patterns, ensure comprehension of and comfortability with wearing the headband; additionally, this will confirm subquality sleep pre-intervention to satisfy eligibility criteria for those assigned to groups that involve the sleep intervention.

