#### Baseline and follow-up visits

Data will be collected at baseline, biweekly, and at the 8-week follow-up to assess changes in sleep, exercise, biomarkers, and cognition. After consent and randomization, participants will be onboarded in person to each intervention-specific device and observed for a 7-day period prior to the baseline visit to establish baseline sleep patterns and/or physical activity levels relevant for each assigned intervention and to ensure all eligibility criteria are satisfied. Cognitive function will be measured using an augmented reality-based tool at baseline and week 8, with brief pulse assessments administered twice-weekly throughout the intervening period. Blood biomarkers will be collected via venipuncture at Quest Diagnostics (baseline and week 8). Physical activity and sleep data will be respectively monitored using Fitbit (all groups) and the Elemind headband (sleep and sleep + exercise groups), and light exposure will be tracked via the Lys device (sleep and sleep + exercise groups). Participants will also complete validated self-report surveys (e.g., PASE, CHAMPS–MET, PROMIS instruments) to capture psychosocial and behavioral variables at weeks 0 and 8. This multimodal approach will enable temporally-aligned, comprehensive data capture across digital and self-reported domains (see Table 3).

**Table 3 Tab3:** Timeline of questionnaires provided

Variable	Screening	Baseline	8-week
Basic Info Screening Form (eligibility criteria)	X		
Physical Activity Readiness Questionnaire (PAR-Q)	X		
Quick Mild Cognitive Impairment screen (QMCI), 6-item	X		
Demographic Questionnaire		X	
Chronic Health Questionnaire		X	X
PROMIS Self-reported Cognitive Functioning Behaviors Short Form		X	X
PROMIS Sleep Disturbance 4a		X	X
PROMIS Emotional Support 4a short form		X	X
PROMIS Depression 4a shot form		X	X
PROMIS Anxiety 4a short form		X	X
PROMIS Social Isolation 4a		X	X
General PROMIS Life Satisfaction 5a		X	
Cross Ethnic-Racial Identity Scale		X	
PASE Physical Activity Questionnaire (exercise and sleep + exercise interventions only)		X	X
CHAMPS-MET Physical Activity Questionnaire (exercise and sleep + exercise interventions only)		X	X

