Participants will begin with a 7-day onboarding period, during which participants will wear the Fitbit continuously to establish baseline physical activity levels and to ensure initial eligibility criteria are satisfied. Subsequent to this initial observation and screening phase, subjects will participate in biweekly, in-person exercise sessions, which will be comprised of 60 minutes of stretching, aerobic, and resistance training exercises. Specifically, exercise sessions will consist of a 10-minute warm-up, followed by 20 minutes of moderate-intensity aerobic exercise at 60–75% of estimated maximum heart rate (MHR). MHR will be estimated using Tanaka’s formula (maxHR = 208-(0.7*age)) [33], and the target heart rate (THR) will be calculated using Karvonen’s formula to account for resting heart rate (RHR), where THR = ((MHR-RHR)*% intensity) + RHR [34]. Moderate-intensity aerobic training will be followed by 20 minutes of resistance training of major muscle groups with an emphasis on lower extremity resistance training one day each week and upper extremity resistance training at the second in-person session weekly. Exercise load will be at 60–80% of an estimated one repetition max using American College of Sports Medicine Guidelines [35]. Muscle groups that will be trained include biceps, triceps, deltoid, and latissimus dorsi for the upper extremity, and quadriceps, hamstrings, and gastrocnemius/soleus for the lower extremity. Resistance training exercises targeting the trunk will also be incorporated. Each exercise session will then conclude with 10 minutes of post-exercise stretching.

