#### Analysis plan

This study is designed as a three-arm, parallel-group trial comparing the effects of an 8-week exercise intervention (group 1), sleep intervention (group 2), and combined sleep + exercise intervention (group 3) on cognitive performance and biomarkers for brain and cardiometabolic health in older adults with MCI or no cognitive impairment. A total of 60 participants (20 per group) will be enrolled. All analyses will be conducted using IBM SPSS Statistics (Version 31.0.0.0; IBM Corp., Armonk, NY, USA). The primary analytic goal is to determine which intervention arm may demonstrate the greatest improvements in cognitive function and biomarker profiles. Descriptive statistics (means, standard deviations, medians, interquartile ranges, and proportions) will be used to summarize demographic characteristics, intervention adherence, and baseline measures. Primary outcomes will include change**s** in cognitive domain-specific and global cognition scores from the digital cognitive assessments and changes in biomarkers for brain (NfL) and cardiometabolic health (HbA1c, hs-CRP, C-peptide, insulin, total cholesterol, HDL, LDL, triglycerides). Secondary outcomes will include changes in sleep metrics (e.g., sleep efficiency, SWS, REM sleep, and total sleep durations, onset latency, and restlessness, as measured via Elemind) and physical activity/exercise levels (PGE and NPA via Fitbit). Tertiary outcomes will include the role of light exposure (measured via Lys) as a potential modulator of sleep parameters and psychosocial measures (e.g., PROMIS Depression, Social Isolation).

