Clinically, this study fills a critical gap by targeting a middle-aged and aging population who have greater cognitive vulnerability to AD. The trial moves beyond self-reported behaviors to integrate real-time, ecologically valid assessments of physical activity, sleep, and cognitive function. In addition, the use of the Digital Neuro-Signature Platform, an innovative Food and Drug Administration Breakthrough Device that deploys augmented reality to evaluate cognitive performance in realistic virtual tasks, marks a significant methodological advancement. The augmented reality-based digital cognitive and functional assessment’s ability to simulate real-world scenarios in order to test higher-order cognitive performance, such as memory, navigation, and object placement, offers a nuanced and sensitive measure of cognitive function that surpasses traditional pencil-and-paper tests, especially for detecting early, subtle impairments [64, 66].

Moreover, the study will incorporate light exposure, which will be captured via the Lys device, as a covariate and potential effect modifier. Light is a critical zeitgeber that regulates circadian rhythms, thereby influencing sleep quality and exercise levels [67, 68]. By capturing ambient light exposure, this study will be able to utilize an improved modeling approach to more robustly test how environmental context modulates interventional efficacy and contributes to individual variability in response. This multidimensional measurement strategy will enhance the rigor and ecological validity of the study, essentially intersecting cognitive neuroscience, digital health, and precision prevention.

From a public health perspective, this trial reflects an innovative shift toward digitally enabled, lifestyle-based interventions for cognitive, brain, and cardiometabolic health. Although the exercise intervention utilized in this trial will be conducted in-person to ensure standardization of procedures, the findings may nonetheless inform future hybridized models of care delivery. The inclusion of wearable sensors (Fitbit and Lys) and neuromodulation technology (Elemind) embodies a next-generation toolkit for behavioral clinical trials. These tools will allow for fine-grained, longitudinal monitoring of physiological, behavioral, and cognitive data with minimal participant burden—an essential consideration for older adults, particularly those with cognitive impairment.

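### Baseline sleep metrics are listed as a model covariate but come from a headband the exercise-only arm does not wear, and the covariate list disagrees with the stated primary model

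*Protocol article*

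**What the plan says.** The covariate list is in Adherence and engagement, under Interventional group 1 (exercise only). It is worded without condition and covers age, sex, education, employment, then "socioeconomic status, baseline sleep metrics, baseline physical activity levels, and cognitive status as covariates".

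On where sleep data come from:

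- Study design overview: "the sleep-only and sleep + exercise groups will receive the Elemind Neuromodulation headband for personalized acoustic stimulation".
- Screening and consent, on the 7-day run-in: "those assigned to sleep or sleep + exercise intervention will receive an Elemind Neuromodulation headband to be used daily without stimulation".
- Baseline and follow-up visits: "Physical activity and sleep data will be respectively monitored using Fitbit (all groups) and the Elemind headband (sleep and sleep + exercise groups".
- Interventional group 1, on its own run-in: "participants will wear the Fitbit continuously to establish baseline physical activity levels".
- Analysis plan, listing the sleep outcomes: "onset latency, and restlessness, as measured via Elemind".

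Measures and instruments makes the same division: Elemind for sleep, Fitbit for activity and heart rate.

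The primary mixed model is specified separately in Analysis plan. Its fixed effects are group, time and group × time, with a random intercept per subject. No covariates are named.

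On missing data, Analysis plan relies on maximum likelihood within the mixed models. Missing data and adherence (under Interventional group 2) rules out multiple imputation and allows pattern mixture modelling or last observation carried forward.

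**The concern.** A covariate can be used in a between-arm model only if it is measured in every arm. Here one listed covariate is absent by design in one arm of three. Mixed-model software keeps subjects with missing outcomes but discards records with a missing fixed covariate. The adjusted model would therefore silently become a comparison of sleep-only with combined.

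The arm at risk matters. Exercise-only against combined shows what the sleep intervention adds to exercise, and exercise-only against sleep-only compares the two single interventions. Both contrasts belong to the stated aim of finding which arm improves most.

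The covariate is also not an idle one. Only participants assigned to a sleep arm are screened for poor sleep, and good sleepers found there may be moved to exercise-only. Baseline sleep is therefore likely to differ between arms, and someone will want to adjust for it.

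**Working it through.** **Inputs.** 20 participants per arm, 60 in total (Power and sample size considerations). Headband at baseline: sleep-only yes, combined yes, exercise-only no (Study design overview; Screening and consent). Two time points, baseline and week 8.

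**Step 1: who has the covariate, with no reassignment.** Sleep-only 20 + combined 20 + exercise-only 0 = 40. Lost: 60 − 40 = 20, and 20/60 = 33%.

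**Step 2: what remains of the test.** With three arms the group × time term has 3 − 1 = 2 degrees of freedom; with two arms it has 2 − 1 = 1. Of the three pairwise contrasts, only sleep-only against combined can be estimated. A check on simulated data of this shape retained 80 records (40 × 2) of the 120 expected (60 × 2), with none from exercise-only.

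**Step 3: allow for reassignment.** Screening and consent permits good sleepers found in a sleep arm to be moved to exercise-only. They bring seven headband nights with them. If k such people join and final arm sizes stay at 20, complete cases are k / 20 / 20. The article gives no k. For illustration only, k = 3 leaves 3 / 20 / 20 = 43 of 60 (86 records in the simulated check), and 17/60 = 28% are lost. The 2-df test can then be fitted, but exercise-only is represented solely by people who met the article's definition of adequate sleep, while the other two arms contain only people who did not. The adjusted contrast would compare groups selected on opposite sides of the covariate itself.

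**Step 4: can a stated method recover the arm?**

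- Maximum likelihood within a mixed model uses incomplete outcome series; it does not supply a missing fixed covariate.
- Multiple imputation is excluded. It would in any case have no data from never-screened exercise-only participants to rest on.
- Last observation carried forward needs an earlier observation, and there is none before baseline.
- Pattern mixture modelling, as described, varies assumptions about missing data for intervention effects; it does not create a baseline predictor.

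**Step 5: set the two model statements side by side.** Adherence and engagement: covariates included, models unspecified. Analysis plan: primary model specified, covariates absent. Under the second statement alone, all 60 participants, 2 degrees of freedom and three contrasts are kept. Nothing in the article says which governs.

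**On power.** I have not turned the loss into a power figure, because the stated 60–65% does not reproduce from its stated inputs by simple routes. For an F test on change scores with λ = f² × N and 2, 57 degrees of freedom, f² = 0.25 gives λ = 15 and 93.2%. Reading the effect as f = 0.25 gives λ = 3.75 and 37.4%. That is a separate matter, and nothing in this point depends on it.

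**The case against.** The strongest reply is that the primary analysis is untouched. The main efficacy test is the group × time term in a model with no listed covariates, and the fallback ANCOVA names only the baseline score. This stands. A reader might infer that the trial cannot answer its primary question; the article does not support that, because the harm follows only if the covariate list is read into the primary model.

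Second, a reader might infer that exactly 0 of 20 exercise-only participants would have the covariate. Reassignment means the number need not be zero, so total loss is the limiting case. The alternative is a biased remnant, not a rescue.

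Third, the covariate sentence does not define baseline sleep metrics. Every arm completes PROMIS Sleep Disturbance 4a at baseline and the Fitbit is worn at night. The exclusion criterion on adequate sleep is also written without reference to arm, although Screening and consent limits it to those assigned to sleep arms. A fuller protocol might define the covariate differently. But the article uses sleep metrics for Elemind output, sorts Fitbit data into activity domains only, and nowhere names the PROMIS score as this covariate.

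Fourth, the Discussion says the study "will incorporate light exposure, which will be captured via the Lys device, as a covariate and potential effect modifier", and the Lys sensor is also confined to the two sleep arms. A reader might infer a second covariate that deletes exercise-only. That is not supported: Objectives and Analysis plan treat light as a modulator of sleep parameters, which are measured in the same two arms, so that analysis loses nobody.

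**Conclusion.** The concern holds for covariate-adjusted three-arm models. Fitted with Elemind baseline sleep metrics, such a model loses about 20 of 60 participants (33%), essentially the whole exercise-only arm. Both exercise-only contrasts become inestimable, or biased if a few reassigned good sleepers remain. The unadjusted primary model keeps all three arms, so the second defect is that two sections of the article disagree on whether the models carry covariates.

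This rests on three assumptions: that baseline sleep metrics means headband output, as elsewhere in the article; that standard mixed-model handling of missing covariates applies; and that reassignments into exercise-only are few, their number not being given.

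Severity: should-fix. The trial is an exploratory pilot, the stated primary model can be fitted, and the correction is short. Left alone, it invites a choice of covariates after the data are seen.

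**What to change.** 1. Reconcile Adherence and engagement with Analysis plan: state which models carry the covariate set, and whether the primary group × time model is adjusted.
2. Remove Elemind baseline sleep metrics from every three-arm model and confine them to analyses of the sleep-only and combined arms.
3. If a sleep covariate is kept in three-arm models, name the baseline PROMIS Sleep Disturbance 4a score, which Table 3 schedules without restriction by arm. Dropping the sleep covariate from three-arm models would also resolve the missing-data problem, but would leave any between-arm difference in baseline sleep unadjusted.
4. As a minor clarification, state that Lys light exposure enters only sleep analyses in the two arms that wear it.

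The cost is a few sentences and no new data. The drawback of the PROMIS score is that it is self-reported: it captures perceived disturbance and not duration, efficiency or staging, so adjustment for device-measured sleep would be available only in the two-arm analyses.
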